#### Plans to promote participant retention and complete follow-up {18b}

To reduce dropout and missing data, reminders to participate in the intervention and monetary reimbursement of participants for the completion of each assessment (€35 per assessment) will be realized continuously.

#### Data management {19}

The data management will be performed at the Centre for Interdisciplinary Addiction Research (CIAR) at the University of Hamburg, Germany, which has successfully coordinated a substantial number of clinical studies as well as large multi-center trials. CIAR is responsible for the installation and monitoring of an overarching data handling concept and the integration of institutional policies of all project partners. An international advisory board will provide advice on methodology. Data integrity and plausibility will be assured by a combination of (i) tailored sets of suitable (and documented) algorithms and (ii) data rating by project associates following a protocol (including the rating of text entry). The Department of Medical Biometry and Epidemiology at the University Medical Centre Hamburg-Eppendorf will conduct the statistical analysis.

#### Confidentiality {27}

All study-related information will be stored securely at the study site. All participant information will be stored in locked file cupboards, and only the study personnel will have access to the cupboard. All reports and administrative forms will be identified by the 6-digit identification (ID) number to maintain participant confidentiality. All records that contain names or other personal identifiers, such as locator forms and informed consent forms, will be stored separately from the study records identified by code number. Personal data will not be transferred to the coordinating body except when necessary in the case of an SAE. All local databases will be secured with password protection. Documents that link participant ID numbers to other identifying information will be stored in a separate, locked file.

The study data will be collected anonymously via tablets. Anonymization will be implemented in accordance with the German Federal Data Protection Act. Each study participant will receive a 6-digit identification (ID) number. The anonymized data will be stored on a secure server of CIAR, which will perform research data management and data cleaning. Access to research data will only be granted to the staff involved in the cleaning and analysis of research data. Project partners will delete all personally identifiable data 5 years after the completion of the project.

#### Plans for collection, laboratory evaluation, and storage of biological specimens for genetic or molecular analysis in this trial/future use {33}

There will be no biological specimens collected.

## Statistical methods

### Statistical methods for primary and secondary outcomes {20a}

#### Primary data analysis

Data on all randomized study participants will be analyzed on an intention-to-treat basis. A mixed model for repeated measures (MMRM) will be applied, using the mean of all measured post-training scores of the outcome, adjusted for the pre-test score (alpha = 0.05, two-sided).

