### Trial design {8}

This study is a multicenter, randomized controlled, outcome adjudicator-blinded superiority trial with two parallel groups and a primary endpoint of psychological distress post-treatment to compare the effectiveness of STARC SUD (“Skills Training in Affect Regulation – a culture-sensitive approach”) versus treatment as usual in trauma-exposed refugees with substance use problems. The randomization will be performed in blocks of 8 with a 1:1 allocation to one of the two treatment arms. Randomization numbers will be assigned to eligible study participants in ascending order of their inclusion.

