#### Intervention description {11a}

The intervention (STARC-SUD) is tailored to the needs of refugees with SUD and additional psychological distress. STARC-SUD is an adaption of Skills-Training of Affect Regulation – a Culture-sensitive Approach (STARC) [10], a culturally sensitive group intervention developed for refugees in Western middle- or high-income countries. The intervention is based on elements from skills-based treatments (e.g., Skills Training in Affective and Interpersonal Regulation therapy (STAIR [11];), Dialectic Behavioral Therapy (DBT [12];), and Culturally Adapted Cognitive Behavioral Therapy (CA-CBT [13];)). The authors developed the STARC program according to guidelines for developing culturally sensitive interventions [14]. The manual includes culture-sensitive metaphors and expressions and uses easy language. A pilot study on Afghan refugees indicated preliminary evidence that the intervention reduces difficulties in emotion regulation, general distress, and post-traumatic stress disorder symptoms [9].

For this trial, STARC was adapted for refugees with SUD [15]. The conceptual framework of Heim and Kohrt was used for the adaptions [16]. The results of five focus group discussions with refugees on concepts of SUD and their treatment informed the adaption. An expert group suggested adaptions and decided by consensus on their implementation. Two pilot groups were conducted with the adapted STARC-SUD program. Interviews with the therapists of these pilot groups informed further adaption.

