#### Sample size {14}

*N* = 286 participants are planned to be included in the study. An earlier RCT comparing a transdiagnostic group intervention for refugees vs. treatment as usual found a greater reduction in psychological distress (as measured by GHQ-12) in the intervention group compared with the control group, with a medium effect size of *d* = 0.57 in the change from baseline to 3-month follow-up [23]. A pilot study of STARC showed that the recruitment of refugees with psychological distress was feasible, with about 85% of the screened patients being eligible for the study [9].

In a previous study evaluating the effects of an integrated present-focused treatment of SUD and PTSD, we found a greater reduction in psychological distress (as measured by SCL-27) in the intervention group compared with the control group, with a mean effect size of *d* = 0.39 [6]. On the basis of these results, we assume a small to medium effect size of *d* = 0.40 for STARC-SUD compared to TAU in a sample of refugees with SUD and co-occurring psychological distress. To detect between-group differences of an effect size of *d* = 0.40 (*α* = 0.05; power = 0.80), 100 participants per group are required. To account for a dropout rate of 30%, we aim to recruit 286 participants.

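### The sample size makes no allowance for therapy-group clustering in the STARC-SUD arm, and the primary model as described names no therapy-group term

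*Protocol article*

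**What the plan says.** The Abstract calls STARC-SUD a group therapy delivered by therapists with interpreters. Intervention description {11a} says that it adapts STARC, "a culturally sensitive group intervention developed for refugees in Western middle- or high-income countries", and was tried out in two pilot groups. Allocation is by individual participant: under Trial design {8}, "The randomization will be performed in blocks of 8 with a 1:1 allocation to one of the two treatment arms". The comparator is whatever care the participant would usually receive, with no trial intervention added (Explanation for the choice of comparators {6b}).

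Sample size {14} gives all its inputs: an "effect size of *d* = 0.40 for STARC-SUD compared to TAU", alpha 0.05 and power 0.80, from which "100 participants per group are required". It then adds: "To account for a dropout rate of 30%, we aim to recruit 286 participants". It mentions no group size, ICC or design effect.

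Primary data analysis, under {20a}, is one sentence. It names an MMRM "using the mean of all measured post-training scores of the outcome, adjusted for the pre-test score", at two-sided alpha 0.05. It names no term for therapy group, therapist or site.

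**The concern.** Men treated in the same therapy group share peers, a therapist and an interpreter, so their post-treatment GHQ-12 scores are likely to be positively correlated. The trial creates no such groups in the usual-care arm. This is a partially nested design: individual randomisation, with clustering that arises after randomisation in one arm.

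For any positive correlation, the mean of the STARC-SUD arm has a larger variance than independent observations would give. A model without a group term then reports too small a standard error, and a group or therapist effect can be read as an intervention effect. A model with a group term is valid but has less power than the sample size section implies. This matters because it is the trial's primary efficacy test.

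**Working it through.** **Inputs from the article:** d = 0.40, two-sided alpha 0.05, power 0.80, 100 analysed per arm, dropout 30%, allocation 1:1.

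**Assumptions, because the article gives no values:** m = 4 to 10 analysed members per therapy group; ICC = 0.01 to 0.10; no clustering under usual care; total variance 1 in both arms.

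**1. The stated figure.** The normal approximation gives n = 2 × (1.960 + 0.842)² / 0.40² = 98.1, so 99 per arm. The noncentral t distribution gives power 0.7997 at 99 and 0.804 at 100, hence 100 per arm. Dropout: 200 / 0.70 = 285.7, so 286. The figures reproduce exactly under independence and leave no room for a design effect.

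**2. Formulas with clustering in one arm.**
- Design effect in the STARC-SUD arm: DE = 1 + (m − 1) × ICC
- Standard error assumed: SE₀ = √(2/100) = 0.1414
- True standard error: SE₁ = √((1 + DE)/100)
- Type I error if groups are ignored: 2 × [1 − Φ(1.96 × SE₀/SE₁)]
- Power if groups are ignored: Φ((0.40 − 1.96 × SE₀)/SE₁)
- Power if groups are modelled: Φ(0.40/SE₁ − 1.96)
- N to restore the design: 100 × (1 + DE)/2 per arm, rounded up, then doubled and divided by 0.70

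For m = 8 and ICC 0.05: DE = 1.35 and SE₁ = √0.0235 = 0.1533. The type I error if ignored is 2 × [1 − Φ(1.808)] = 7.1%. Power if modelled is Φ(2.609 − 1.96) = 74.2%.

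| m | ICC | DE | Ignored: type I error | Ignored: power | Modelled: power | N to restore |
|---|---|---|---|---|---|---|
| 4 | 0.01 | 1.03 | 5.2% | 80.6% | 80.2% | 292 |
| 10 | 0.01 | 1.09 | 5.5% | 80.2% | 79.0% | 300 |
| 4 | 0.05 | 1.15 | 5.9% | 79.9% | 77.9% | 309 |
| 6 | 0.05 | 1.25 | 6.5% | 79.4% | 76.0% | 323 |
| 8 | 0.05 | 1.35 | 7.1% | 78.8% | 74.2% | 338 |
| 10 | 0.05 | 1.45 | 7.7% | 78.4% | 72.4% | 352 |
| 8 | 0.10 | 1.70 | 9.2% | 77.3% | 68.2% | 386 |
| 10 | 0.10 | 1.90 | 10.4% | 76.5% | 65.1% | 415 |

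The two *Ignored* columns belong to one analysis and the *Modelled* column to another. These are large-sample figures. With 100/10 = 10 to 100/4 = 25 groups, small-sample degrees of freedom would lower the modelled power a little further.

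**3. Credit for the pre-test score.** Suppose d = 0.40 is on the unadjusted scale and adjustment scales the whole variance by 1 − r². At m = 8, ICC 0.05 and an assumed r = 0.5, the variance is 0.0235 × 0.75 = 0.0176 and power is about 85%. At m = 10 and ICC 0.05, the loss is offset when 2.45 × (1 − r²) = 2, that is r = 0.43. This is the favourable case. If the group effect arises during therapy, the pre-test score cannot explain it. The first variance is then (2 × 0.75 + 7 × 0.05)/100 = 0.0185, with power about 84%. Adjustment can therefore recover power. It does not repair the type I error, because the group component stays in the residual.

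**4. Plausible group size.** Recruitment {15} plans about 4 randomised participants per site per quarter, so about 2 to STARC-SUD. With 30% dropout, 4 analysed members need 4/0.70 = 5.7 randomised, or about 9 months of one site's STARC-SUD accrual. Eight need 8/0.70 = 11.4, or about 17 months. If groups are closed, site-based and made up only of trial participants, the smaller sizes are more plausible.

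**The case against.** A reader might infer that the primary model treats participants as independent, so that the 5% error rate and the 80% power both fail. The article does not support this, for four reasons.

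- **The model half rests on silence.** The one-sentence description also leaves out the time term and the covariance structure, so it is not a complete list of terms. A fuller analysis plan may contain a group effect, and nothing shows that group membership will go unrecorded. This stands, and it is why the fix accepts a confirmation.
- **The size is assumed.** Neither m nor the ICC is in the article. At ICC 0.01 the type I error is 5.2% to 5.5% and the modelled power 79.0% to 80.2%, so little is lost. The accrual plan favours small groups, and allocated men who never attend a group dilute the clustering in an intention-to-treat analysis. This stands too.
- **The two failures are alternatives.** Ignoring groups leaves power at 76.5% to 80.6% and damages the error rate. Modelling them protects the error rate and costs power. No single analysis suffers the full extent of both.
- **Pre-test adjustment may restore the power.** That is so for a moderate pre-post correlation, but the article takes no explicit credit for it, and it does not mend the error rate.

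The format of usual care is also not described. Treating that arm as unclustered is an assumption, though the trial itself creates no groups there.

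None of this reaches the sample size. Its inputs are complete and published, and its result is the independent-participants figure. An analysis plan that is not shown cannot change that.

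**Conclusion.** The point holds in conditional form. It is certain that the 100 per group and 286 in total allow nothing for therapy-group clustering, although one arm is treated in groups under individual randomisation. It is also certain that the described primary model names no therapy-group term. If the model were run as described, the standard error would be too small for any positive ICC.

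The size depends on values that the article does not give. In the two middle cases, m = 4 and m = 8 at ICC 0.05, ignoring groups gives a type I error of 5.9% or 7.1%. Modelling them gives power of 78% or 74% before credit for the pre-test score. The documents do not establish that the final analysis will ignore groups, or that power will fall below 80% once pre-test adjustment is counted.

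**What to change.** In Sample size {14}, state the expected number of analysed members per therapy group and an ICC range, for example 0.01 to 0.10. Restate the power for 286 participants over that range, with and without credit for pre-test adjustment, giving the assumed pre-post correlation.

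In Primary data analysis, specify a partially nested model, or confirm that the analysis plan already has one. It should have a random therapy-group effect in the STARC-SUD arm only, arm-specific residual variance, and Satterthwaite or Kenward-Roger degrees of freedom. Usual-care participants, and STARC-SUD participants who never attend a group, are treated as their own clusters. Record a therapy-group identifier for every STARC-SUD participant. Recruitment has already begun, so this field should be secured now.

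The cost is some added wording, one data field, a somewhat wider confidence interval and a less favourable stated power. No extra patients are needed, because the request is to restate the power and not to enlarge the trial. The identifier reveals the arm to the analyst, whom Implementation {16c} keeps unaware of assignment, so the analysis code should be fixed before database lock.

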## Methods: participants, interventions, and outcomes

### Study setting {9}

Participants will be recruited in six metropolitan regions of Germany (Hamburg, Bremen, Berlin, Hannover, Frankfurt, München). The intervention is conducted in SUD counseling and treatment centers in the six metropolitan regions.

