#### Recruitment {15}

To include 286 individuals, participants will be recruited from SUD counseling and/or treatment centers in 6 metropolitan regions of Germany (Hamburg, Bremen, Berlin, Hannover, Frankfurt, München). Participants will be recruited by promotional print material, videos, blogs, personal presentations in refugee camps, SUD treatment, and counseling centers, via advertisements in magazines, on websites, and on social media.

Assuming that about two-thirds (67%) of the screened refugees will be eligible, and about two-thirds (67%) of the eligible refugees will agree to participate, approximately 5 refugees per month need to be screened in each center, and about 4 participants per quarter (16 per 12 months) need to be randomized at each of the 6 sites to include 286 patients. The approx. enrollment period will span 36 months.

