### Assignment of interventions: allocation

#### Sequence generation {16a}

The allocation sequence was generated by computer-generated random numbers using R. Participants are randomly assigned to either the control or the experimental group with a 1:1 allocation as per a computer-generated randomization schedule stratified by site using blocks of random sizes. The block sizes will not be disclosed to ensure concealment.

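### Randomisation is stratified by site, but the stated primary model adjusts only for the pre-test score; adding site is a free improvement, minor in size

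*Protocol article*

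**What the plan says.** Sequence generation {16a} describes a "computer-generated randomization schedule stratified by site using blocks of random sizes". Recruitment {15} gives the number of strata: about four participants per quarter "need to be randomized at each of the 6 sites to include 286 patients". Study setting {9} confirms that treatment is delivered locally: "The intervention is conducted in SUD counseling and treatment centers in the six metropolitan regions".

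The primary model is described once, under Primary data analysis in section {20a}: "A mixed model for repeated measures (MMRM) will be applied, using the mean of all measured post-training scores of the outcome", and this is "adjusted for the pre-test score (alpha = 0.05, two-sided". Site is not mentioned there or anywhere else in the statistical sections. The text does not say that site is excluded.

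Trial design {8} describes the randomisation differently: "The randomization will be performed in blocks of 8 with a 1:1 allocation to one of the two treatment arms". It names no stratification factor and gives a fixed block size, where {16a} speaks of random, undisclosed sizes. The two descriptions should be reconciled. I take {16a} as the operative statement on stratification because it is the section devoted to the sequence, and {8} does not deny stratification.

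**The concern.** Balancing the arms within each site removes between-site differences from the true sampling error of the treatment difference. A model without site leaves those differences in its residual variance. The estimated standard error then exceeds the true one, as far as the strata are concerned, whenever site predicts the outcome beyond the pre-test score.

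That is plausible here, though not shown. The comparator is the usual care of local counseling and treatment centers or general practitioners across six cities. Outcomes are also collected locally, with help from site staff and translators.

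At stake are a slightly wide confidence interval, a test slightly below its nominal level, and some efficiency that the stratified design already makes available. Validity is not threatened by this mechanism.

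**Working it through.** **Inputs from the protocol article.** Six sites; 1:1 allocation; d = 0.40; two-sided alpha 0.05; power 0.80; 100 per group analysed; 30% dropout; 286 recruited.

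**Input not given.** The site share r of the residual variance after baseline adjustment. I assume 0 to 0.10.

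**1. The plan's own figure.** The two-sample normal formula gives 99 per arm, and the t-test version 99.08, rounded up to 100. Power at 100 per arm is 0.807 (normal) or 0.804 (t). 200 / (1 − 0.30) = 285.7, so 286. The stated sample size reproduces.

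**2. Closed form, with perfect balance within sites and total residual SD 1.**

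- Standard error that the model without site reports: √(2/100) = 0.1414.
- True standard error: 0.1414 × √(1 − r).
- Overstatement: 1/√(1 − r).
- Actual two-sided alpha: 2 × [1 − Φ(1.96/√(1 − r))].
- Power without site: Φ[(0.40 − 1.96 × 0.1414) / (0.1414 × √(1 − r))].
- Power with site: Φ[0.40 / (0.1414 × √(1 − r)) − 1.96].

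| r | SE overstated by | Actual alpha without site | Power without site | Power with site | Points forgone |
|---|---|---|---|---|---|
| 0 | 0% | 0.050 | 0.807 | 0.807 | 0 |
| 0.01 | 0.5% | 0.049 | 0.809 | 0.811 | 0.2 |
| 0.02 | 1.0% | 0.048 | 0.810 | 0.815 | 0.5 |
| 0.05 | 2.6% | 0.044 | 0.814 | 0.827 | 1.3 |
| 0.10 | 5.4% | 0.039 | 0.820 | 0.846 | 2.6 |

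**3. Simulation without dropout.** ANCOVA with six sites, 34 per site, blocks of 8 with an incomplete last block, 6,000 runs, no treatment effect.

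- r = 0.10, site omitted: mean model SE 0.1203 against an empirical SE of 0.1170. The ratio is 1.028, so 2.8% too large; rejection rate 0.043.
- r = 0.10, site included: 0.1152 against 0.1168; rejection rate 0.051.
- r = 0.05, site omitted: 0.1209 against 0.1207; rejection rate 0.049.

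The relative Monte Carlo error of an empirical SE is about 1/√(2 × 6,000) = 0.9%, so the results at 5% are hard to tell from no effect.

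**4. Simulation with 30% random dropout.** Six sites, 48 per site, 10,000 runs, no baseline covariate.

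- r = 0.05: SE about 1% too large, alpha 0.048, power 0.816 without site and 0.828 with it.
- r = 0.10: SE about 2 to 2.5% too large, alpha 0.043, power 0.812 without site and 0.838 with it.

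The closed-form figures for SE and alpha are therefore upper bounds, because incomplete blocks and dropout disturb the balance and cut the distortion to roughly half. The power differences (1.2 and 2.6 points) agree with the closed form, because site in the model also corrects the chance imbalance.

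**5. A force in the other direction.** STARC-SUD is given in groups. The simulation in step 3, with an assumed therapy-group intraclass correlation of 0.05 and assumed groups of 8, gave rejection rates without site of 0.066 (r = 0.05) and 0.073 (r = 0.01), above nominal. With site they were 0.070 and 0.076. Site adjustment does not deal with that clustering.

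**The case against.** The strongest reply is that a short journal description is being read as a complete covariate list. The two sentences also leave out the covariance structure and other model terms, the analysis plan is not shown, and nothing excludes site. It stands that a reader may not infer a deliberate decision to leave site out. It does not remove the point: the article goes as far as stating the adjustment, and that adjustment lacks the stratification factor. An analysis that follows it would carry the omission forward. If the analysis plan already includes site, only the published statement needs aligning.

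The size is also open to challenge, and here the objection largely stands. The site share is assumed and may be zero. Baseline GHQ-12 may absorb some site differences. The article does not say that usual care differs by region, and if it did, part of that would be variation of the treatment effect between sites, which a site main effect captures only partly.

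A reader might infer that the trial's standard errors are too large and its test conservative overall. The documents do not support this, because clustering by therapy group may push the other way and its size is not given. A reader might also infer that the trial falls short of its planned power. It does not for this reason: every power figure without site above exceeds 0.80.

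**Conclusion.** The mismatch between the stratified allocation and the stated model is real, and its direction is clear for the strata taken alone: conservative, with a little power forgone. Between a site share of 0% and 10%, the power forgone runs from 0 to about 2.6 points. The overstatement of the standard error runs from 0% to at most 5.4%, and roughly half that under incomplete blocks and dropout.

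This rests on an assumed site share, on allocation having been stratified as {16a} states, and on about 100 analysed per arm. The point says nothing about the net error of the trial, since therapy-group clustering is a separate issue. It is a free improvement, minor in size.

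**What to change.** Add site (six levels) as a fixed effect to the primary MMRM, alongside the pre-test score, and to the same model for the secondary outcomes. Record this before the data are analysed, so that the choice cannot look data-driven.

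The cost is one phrase in the model description and 6 − 1 = 5 degrees of freedom out of about 200 analysed participants. With 200/6, or about 33, analysed per site on average, six fixed effects are easily supported. The planned N of 286 does not change.

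In the same edit, reconcile Trial design {8} with Sequence generation {16a} on the stratification factor and the block sizes. Therapy-group clustering needs its own treatment; it is not a reason to leave site out.
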